### Sample size calculation

The sample size is based on detecting a difference in daily PA according to the guideline for moderate intensity PA. Previous PHSs (2005) showed that 38% of construction workers with an elevated CVD risk was physically inactive according to this guideline. To show a 10% difference between the intervention and the control group after 26 weeks, i.e. 38% inactivity in the control group and 28% inactivity in the intervention group, with a power of 80% and a 95% confidence interval (α = 0.05), 692 persons will be needed (346 in each group). As we expect a loss to follow-up of 20%, 866 persons will be included at baseline. Based on an assumed initial non-response of 50%, we will invite 1,732 workers. In The Netherlands, each month approximately 3,334 workers are screened in a PHS. Based on PHS data obtained in 2006, we expect that on average approximately 667 of them (20%) will fulfil the inclusion criteria. Therefore, we expect that the recruitment period will last at least 3 months. The numbers are presented in Figure 1.

**Figure 1 F1:**
[figure not shown]
Flow diagram of recruitment of the study population.

### Blinding

The design of the study (individual counselling versus usual care) makes blinding of participants impossible. Neither the counsellors can be blinded. The research assistant will perform the randomisation procedure, and process the follow-up questionnaires. The principal investigator, who is responsible for the data analysis, will thus be blinded for the allocation. In the invitation letter for follow up, the worker will be asked not to reveal his group status to the occupational nurse, so that the latter will be blinded as well. However, there is no guarantee that the occupational nurses will be blinded in all cases.

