### Setting

The study population will be recruited from all Occupational Health Services (OHSs) throughout The Netherlands that perform Periodical Health Screenings (PHSs) in construction industry. A PHS is offered every four years to all construction workers under the age of 40. Workers above the age of 40 are invited for a PHS every two years. All occupational physicians (OPs) and occupational nurses employed at the abovementioned OHSs were invited to apply for the role of lifestyle counsellor in our study. We made a selection based on their motivation, interest in lifestyle, and affinity with the target group.

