### Compliance and loss to follow-up

Except for those who have explicitly stated to leave the study, all participants will receive a questionnaire 26 and 52 weeks after baseline, and an invitation for a health check at the OHS. The number of contacts, as well as loss to follow-up, will be recorded by the research assistant. We will try to avoid or reduce loss to follow-up by various means. For example, each counsellor will have personal contact with his or her own clients. If the client does not show up at the OHS or answer the telephone at the appointed time, the counsellor will call him again to make a new appointment. Furthermore, incentives will be sent to all participants.

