
### Outline of the intervention

The intervention will last 6 months, since this is the minimum amount of time to achieve maintenance of changed behaviour. For the reasons described above, MI will be used as a counselling method. Based on the evidence for the effectiveness of frequent contacts, and on the preferences of the interviewed workers, 3 face-to-face and 4 telephone contacts will be scheduled. The first contact will always be face-to-face. The duration of a face-to-face contact will be 45–60 minutes. The telephone calls will take 15–30 minutes. Face-to-face contacts will preferably take place after participant's working hours (that is: after 3 pm) at the OHS. If a participant explicitly states that he does not want to visit the OHS, the counsellor may arrange a home visit. As suggested by the interviewed workers, the wife or partner of the participant will be invited to accompany the participant to the face-to-face meeting. Additionally, written materials will be provided. The intervention will be performed by 24 counsellors (occupational nurses and OPs) who have been trained for the purpose of this study. Each participant will be in contact with one specific counsellor during the entire intervention. Each participant in the intervention group will be allocated to a counsellor in his own region of residence. The counsellor will strive to arrange the first contact within the first week after inclusion, and arrange further contacts each month, with a margin of one week. The last telephone contact should take place in the 25^th ^week after inclusion at the latest. The schedule for each participant in the intervention group is presented in Table 2.

**Table 2 T2:** Contacts schedule for each participant in the intervention group.

**T in weeks**	**Event**
0	Invitation for first face-to-face encounter.
1	Face-to-face contact
4	Telephone contact
8	Face-to-face contact
12	Telephone contact
16	Telephone contact
20	Face-to-face contact
23	Telephone contact
26	First follow-up measurement
52	Second follow-up measurement.

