#### Biomedical variables

BMI (kg/m^2^), systolic and diastolic blood pressure (mmHg), HDL-cholesterol, total cholesterol (mmol/l) and HbA1c (%) will be assessed by an occupational nurse at the PHS. First, weight will be measured on a digital balance, without shoes and jacket. After that, blood pressure will be measured once, by manual inflation, while the worker is seated. In most OHSs, a Maxi Stabil 3 measuring instrument (Speidel & Keller) will be used for this purpose. Finally, for the determination of HDL-cholesterol, total cholesterol and HbA1c levels venous blood will be drawn from the lower arm and transported to the laboratory for analysis. For each of these 3 measures 1.6 ml blood will be used. As described in the introduction, elevated BMI, blood pressure and cholesterol are indicators of CVD risk. HbA1c, a measure of haemoglobin glycosylation, is an indicator of the mean blood glucose level of the past 6–8 weeks [47]. Elevated HbA1c was shown to be an independent risk factor for coronary heart disease in persons with and without diabetes [48].

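### The stated safeguard for the follow-up nurse's blind (the worker's silence) does not cover a counsellor-nurse who measures a man he or she counselled; the exposure is mainly the single manual blood pressure reading

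*Protocol article*

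**What the plan says.** **Safeguard.** Under Blinding, the article says that participants and counsellors cannot be blinded. For the nurse at follow-up it relies on the invitation letter: "the worker will be asked not to reveal his group status to the occupational nurse, so that the latter will be blinded as well". The next sentence admits that this may not succeed for every nurse.

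**Who counsels.** Under Setting: "All occupational physicians (OPs) and occupational nurses employed at the abovementioned OHSs were invited to apply for the role of lifestyle counsellor". Those are the services that perform the periodic health screenings. Under Outline of the intervention: "The intervention will be performed by 24 counsellors (occupational nurses and OPs) who have been trained for the purpose of this study". The same section adds "Each participant in the intervention group will be allocated to a counsellor in his own region of residence" and "Face-to-face contacts will preferably take place after participant's working hours (that is: after 3 pm) at the OHS".

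**Who measures.** Under Compliance and loss to follow-up, "all participants will receive a questionnaire 26 and 52 weeks after baseline, and an invitation for a health check at the OHS". Under Biomedical variables, BMI, blood pressure, lipids and HbA1c "will be assessed by an occupational nurse at the PHS", and "blood pressure will be measured once, by manual inflation, while the worker is seated". Weight is taken on a digital balance. Lipids and HbA1c come from venous blood sent to a laboratory.

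**Heart rate.** Under Cardio respiratory fitness, resting heart rate is taken by the counsellor at the first meeting and repeated at the 6- and 12-month check-ups in the intervention group only. The measuring procedure in that section has the counsellor reading the value.

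**The concern.** A request to the worker works only if he is the nurse's sole source of information about his group. A nurse who has counselled him already knows it. The plan draws counsellors partly from the occupational nurses of the OHSs that run the follow-up checks, and it states nothing that stops a counsellor from taking the outcome measurements of a client.

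Only intervention men have a counsellor, so any leniency towards one's own clients would enter one arm and favour the intervention. Manual blood pressure, read once, leaves room for rounding and offers no second reading as a check. The behavioural outcomes are self-reported by unblinded men, so the nurse-measured outcomes have value as corroboration. Systolic pressure is also a named effect measure in the cost-effectiveness ratios.

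**Working it through.** **1. Does the safeguard cover this route?** Setting the sections side by side:

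- Counsellor pool: occupational physicians and occupational nurses of the OHSs that run the screenings (Setting; Outline of the intervention).
- Follow-up measurer: an occupational nurse, at the OHS (Compliance and loss to follow-up; Biomedical variables; Blinding).
- Place of counselling: preferably the OHS, with a counsellor from the man's own region (Outline of the intervention).
- Separation rule: none stated.
- Counsellor presence at follow-up: heart rate is repeated at those check-ups in intervention men, and the procedure described has the counsellor reading it (Cardio respiratory fitness). This makes overlap plausible. It does not show that the same person takes blood pressure.

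The answer is no: silence removes one source of knowledge and leaves the other in place.

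**2. The plan's own group size.** The later steps use 346 per group, so I reproduced it first. For 38% against 28%, two-sided alpha 0.05 and 80% power, with mean proportion 0.33:

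n = [1.960 × √(2 × 0.33 × 0.67) + 0.842 × √(0.38 × 0.62 + 0.28 × 0.72)]² / 0.10² = 345.9, so 346 per group and 692 in total. This agrees with the article. With 20% loss, 346/0.8 gives 433 per group, or 866, which also agrees.

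**3. Possible size.** None of these inputs is in the documents: systolic SD 15 mmHg (range 12 to 18), readings 2 mmHg low when a man is measured by his own counsellor, and a share f of intervention men so measured. There is assumed to be no true effect.

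- Standard error of the difference: 15 × √(2/346) = 1.14 mmHg.
- False shift in the group difference: f × 2 mmHg.
- Two-sided type I error: P(|Z + shift/SE| > 1.96).

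| Share f | Shift (mmHg) | Shift/SE | Type I error, SD 15 | SD 18 to SD 12 |
|---|---|---|---|---|
| 10% | 0.2 | 0.18 | 5.4% | 5.2% to 5.6% |
| 25% | 0.5 | 0.44 | 7.2% | 6.5% to 8.5% |
| 50% | 1.0 | 0.88 | 14.2% | 11.3% to 19.5% |

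With readings 4 mmHg low and SD 15, the three rows become 6.4%, 14.2% and 41.8%.

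The plan adjusts for baseline, which narrows the standard error without removing the shift. With an assumed baseline correlation of 0.5, SE = 1.14 × √(1 − 0.25) = 0.99, and a 1 mmHg shift gives 17.3%.

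**The case against.** Several points on the other side have force.

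- **The article concedes imperfection.** It claims an attempted blind and says outright that the blind is not guaranteed. That stands. The concession names no role overlap, however, and brings no rule, record or sensitivity analysis.
- **The roles are named separately.** Blinding treats counsellors and the follow-up nurse as different people, and the cost-effectiveness section costs counselling contacts and nurse check-ups as separate items. This suggests that separation was intended, but it does not require it.
- **The overlap is inferred.** Some of the 24 counsellors are physicians, in an unstated proportion. Allocation is by region of residence, not by the site of the check. No sentence says that counsellors take blood pressure or weight at follow-up. All of this stands, and it limits the claim to what the plan permits.
- **A fuller protocol may hold a booking rule.** It may. The point here is that the article names a specific safeguard and draws from it a conclusion that its own staffing undermines.
- **The reach is narrow.** Weight on a digital balance leaves little room for rounding, and laboratory values and questionnaires depend little on the nurse. The abstract lists blood pressure as secondary, although the section headings place the biomedical variables under the primary outcome measures. The narrow reach stands.

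A reader might infer that the nurse blind cannot hold at all, or that error rates of 14% and above are to be expected. The documents support neither. They do not show that any man is measured by his own counsellor, and the higher rates need an assumed share of half the arm, or a larger assumed bias.

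**Conclusion.** The point holds in limited form. As written, the plan permits a counsellor-nurse to take outcome measurements from a man he or she counselled, and the only stated safeguard does not protect against this. It can happen only in the intervention arm, so any resulting bias would favour the intervention. Blood pressure carries most of the exposure.

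The size cannot be derived from the documents. With 2 mmHg as the assumed bias and SD 15, the type I error runs from barely above nominal (5.4%) when a tenth of the arm is affected, through about 7% at a quarter, to about 14% at a half. The self-reported primary comparisons and the sample size are not touched. The one-arm heart rate measurement can reveal the group to whoever sees it, which is a second route. It is used here only as evidence that a counsellor may be present at the check.

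**What to change.** 1. In Blinding and Biomedical variables, state: 'No counsellor takes blood pressure or weight at 26 or 52 weeks from a man he or she counselled; where staffing allows, no counsellor takes them from any participant.'
2. Record the measurer's ID at every follow-up check, so that it can be matched to the counsellor list. This cannot be reliably reconstructed later.
3. Repeat the blood pressure and BMI comparisons without checks done by a counsellor. This is a sensitivity analysis only, because the exclusions may fall unequally on the two arms.
4. Reconcile Blinding, Biomedical variables and Cardio respiratory fitness on who does what at the follow-up check, including who takes heart rate.

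The cost is a booking rule, one data field and some loss of scheduling freedom at small OHSs. Staffing per OHS is not given, which is why the stricter half of the rule is conditional.

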### Co-interventions

It is likely that some participants, in the intervention group as well as in the control group, will make use of other CVD risk-related health care, such as medication, other types of treatment, or lifestyle advice by another health care professional. Furthermore, some participants in the control group may start changing their lifestyle during the study, after being confronted with their CVD risk. Such 'co-interventions' cannot be avoided and will therefore be assessed in the questionnaires at baseline and follow-up. Use of additional health care as a result of the counselling, e.g. physiotherapy, dietician advice, or nicotine replacement therapy (NRT), will nor be encouraged neither be discouraged per se since it may have beneficial effects on lifestyle that may not be obtained without the intervention.

### Compliance and loss to follow-up

Except for those who have explicitly stated to leave the study, all participants will receive a questionnaire 26 and 52 weeks after baseline, and an invitation for a health check at the OHS. The number of contacts, as well as loss to follow-up, will be recorded by the research assistant. We will try to avoid or reduce loss to follow-up by various means. For example, each counsellor will have personal contact with his or her own clients. If the client does not show up at the OHS or answer the telephone at the appointed time, the counsellor will call him again to make a new appointment. Furthermore, incentives will be sent to all participants.

### Usual care

Since we aim to assess the effectiveness of a lifestyle intervention as compared to usual care, the control group does not receive the intervention of concern neither any addition to usual care except for the follow-up measurements. Thus, each participant in the control group will receive care as usual, provided by his own OP. Usual care for those with an elevated CVD risk consists of informing the worker about his risk profile. This may be done in a brief oral explanation or by post. In some cases, the OP provides brochures about CVD risk factors and/or lifestyle. Whether further care is provided, such as personal lifestyle advice or referral to the general practitioner (GP), depends on the seriousness of the risk and the OP's usual practice.

### Development of the intervention

#### Interviews

Preceding the study, interviews were held with 14 employees, 6 employers and 9 OPs [18]. The aim of those interviews was to get insight in the workers' current lifestyle, their attitudes towards changing behaviour, their preferences for the type of lifestyle intervention and the feasibility of a lifestyle intervention in construction industry. It appeared that white-collar workers in particular reported a lack of regular PA. Most blue-collar workers said to have daily PA at work. However, hardly any of the interviewed workers reported participating in organised sports. In general, the workers thought to have a healthy diet, but some reported to eat large amounts. Most workers had a positive attitude towards a lifestyle intervention, under the condition that participation in the intervention would be voluntary. Most workers said they would prefer at least one face-to-face contact, preferably at the start of the intervention, with a professional health counsellor. As to the frequency of the contacts, most workers suggested about once a month. They were generally positive about additional counselling by telephone. The majority of the workers interviewed thought that brochures about lifestyle would be helpful, if provided additionally. Furthermore, toolbox meetings at work were suggested as a good opportunity for giving lifestyle advice. Email or SMS were not considered as appropriate media. Some of the workers said that they would appreciate involvement of their wives in the intervention, especially if the intervention would focus on a change in dietary behaviour. The 6 employers who were interviewed emphasised that the intervention should not be pedantic, and that the worker should be confronted with his risk profile and the associated negative health consequences. Moreover, the employers agreed that the person carrying out the intervention should be experienced in counselling and he/she should have experience with the target population. From the interviews with the OPs, it was confirmed that there is neither consensus nor a guideline for lifestyle-related health promotion aimed at workers in the construction industry. All of them were enthusiastic about the initiative of developing a lifestyle intervention. To date, OPs hardly perform lifestyle counselling, because of a lack of time, knowledge, and possibilities for follow-up. They suggested linking the lifestyle intervention to the PHS. According to the OPs, the workers' CVD risk should be communicated in a way that is easy to understand, e.g. visually.

Based on the interviews we concluded that the intervention should preferably be linked to the PHS; contain monthly face-to-face and/or telephone contacts with one and the same counsellor; especially focus on PA in leisure time and the amount of dietary intake; involve the workers' partner if possible. Moreover, CVD risk should be communicated in an understandable way.

#### Literature search

A literature search was performed to gain more insight in the effectiveness of previously implemented lifestyle interventions. In the report of Proper et al (2005), especially individually-based lifestyle interventions appeared to be effective [19]. Since we were interested in smoking, diet and PA behaviour in particular, we looked at studies aimed at these three lifestyle factors. For smoking, it has been shown that a minimal contact behavioural intervention using the stage-of-change concept in Dutch general practice significantly improved self-reported abstinence rates at 12-month follow up [20]. Duration and frequency of counselling in a smoking intervention appeared to have a strong dose-response relation with smoking cessation rates [5,21]. However, even though individual counselling is potentially effective in smoking cessation, success rates for smoking cessation and abstinence may be increased by using NRTs, such as nicotine plasters, gum and spray [5]. Concerning dietary behaviour change, Steptoe et al. (1999) showed that brief dietary behavioural counselling led to decreased dietary fat intake among adults with increased CVD risk in general practice [22]. Furthermore, personalised feedback has been shown to improve attitude and intention, and to significantly increase vegetable intake and decrease fat intake among healthy employees [23]. Finally, evidence was found for the effectiveness of individually-based PA interventions, among sedentary adults in general practice [24], as well as in a workplace setting [25]. Individual counselling can be performed in several ways. In recent years, counselling has become more client-centred. One potential effective and client-centred technique is motivational interviewing (MI). MI is a non-directive, client-centred counselling method, which was originally developed for use in addiction interventions [26]. In recent years, it has also been proven feasible and effective in lifestyle interventions [27-29]. According to Rubak *et al.* (2005), the effect of MI increases with an increasing number of face-to-face encounters [30]. MI is based on five principles, i.e. showing empathy, avoiding discussion, rolling with resistance, supporting self-efficacy, and raising awareness of a dissonance between actual behaviour and behaviour goals. Important non-directive communication strategies used in MI are: Asking open questions, reflective listening and orderly summarizing. Providing information, provocation, and selective confirmation are more directive strategies. In MI a fluent continuum of readiness-to-change is presumed [31]. The transtheoretical model (TTM) of stages of change (SOC) has played an integral role in the development of MI. Another model describing the stages of behaviour change that we found in the literature is the Precaution Adoption Process Model (PAPM) [32]. The PAPM distinguishes seven stages: 1) Unaware of the health issue, 2) Aware of the issue but not personally engaged, 3) Engaged in the issue and deciding what to do, 4) Having decided not to act, 5) Planning to act but not yet having acted, 6) Initiating the behaviour, and 7) Having maintained the behaviour over time. In contrast to the TTM, the PAPM distinguishes between stages 1 and 2 and between stages 4 and 5. In a stage-based intervention, in general, persons unaware or unengaged may need to be made more aware of the risks of their own health situation and the possibility of behaviour change. They can be informed, advised and encouraged. With persons in the decision stage, barriers and benefits of behaviour change should be discussed, and 'the positive' should be accentuated. Persons in the preparation stage need to set short-term goals that are acceptable, accessible and effective, taking into account past experiences. Persons who just initiated behaviour change deserve affirmation for what they have accomplished and encouraging comments. They may need assistance in possible revision of their plans. In this stage, anticipation on possible future barriers may also be necessary. The same strategy holds true for persons who have already maintained behaviour over time [33]. Persons who have relapsed into former behaviour need to be guided through the stages again. Persons who have decided not to change a certain (sub-) behaviour may decide to change another (sub-) behaviour. To achieve behaviour change, relevant determinants of behaviour will have to be addressed in the intervention. From the literature we learned that attitude, self efficacy, social influence (the principal components of the ASE-model [34,35]), intention [34,36], environment, and habitual behaviour [37] are important behavioural determinants. Finally, we looked at literature about risk communication. Several studies have shown that the explanation of CVD risk to the patient or client should be clear and easy to understand, to prevent confusion or fear [38] and to enable the client to make a well informed choice about if and what he wants to change [39]. Based on the literature, we decided to develop an individually-based lifestyle intervention, comprising frequent contacts, applying MI, with the PAPM as a basis. Next to the SOC, behavioural as well as environmental determinants will be taken into account during the counselling sessions. The workers' CVD risk will be explained to him in an understandable way.
